## Abstract

**Background:**

Sodium-glucose cotransporter 2 inhibitors (SGLT2i) are considered to have the potential to maintain renal function by correcting glomerular hypertension in patients with diabetic kidney disease (DKD). The aim of this study is to demonstrate the renoprotective effect of SGLT2i by measuring renal hemodynamics, including glomerular filtration fraction (FF), in type 2 diabetic patients with moderate renal dysfunction.

**Methods:**

Renoprotective effect of canagliflozin derived from test of renal hemodynamics in diabetic kidney disease (FAGOTTO) study is a 12-week multicenter, open-label, randomized (1:1), parallel-group trial of type 2 diabetic patients with diabetic kidney disease (30 ≤ estimated glomerular filtration rate [eGFR] ≤ 60 mL/min/1.73 m^2^). A total of 110 patients are to be randomly allocated to receive once-daily canagliflozin 100 mg or control (standard therapy). FF will be calculated by dividing the measured GFR (mGFR) by the effective renal plasma flow (eRPF). mGFR and eRPF will be measured by the clearance of inulin and para-aminohippuric acid (PAH), respectively. The primary endpoint of this trial is the percentage change in FF after 4 weeks of treatment in the canagliflozin and control groups.

**Discussion:**

The FAGOTTO study will elucidate the mechanism of the renoprotective action of SGLT2i. The background, rationale, and study design of this trial are presented. To date, > 80 patients have been enrolled in this trial. The study will end in 2025.

**Trial registration:**

jRCT (Japan Registry Of Clinical Trials) jRCTs041200069. Date of registration: November 27, 2020.

**Supplementary Information:**

The online version contains supplementary material available at 10.1186/s12882-023-03277-0.

## Background

In recent decades, the number of patients with diabetes and prediabetes has increased worldwide [1] as well as in Japan [2]. Diabetes can damage major organs, including the kidneys, and the most serious consequence is end-stage renal disease, which requires renal replacement therapy [3]. A worldwide report revealed that the global annual incidence of end stage-renal disease (ESRD) among patients with diabetes has increased, but interestingly, in one region in Europe, the rate decreased [4]. Diabetic kidney disease (DKD) is the most common primary disease among prevalent and incident dialysis patients in Japan [5]. In addition, the presence of DKD markedly increases cardiovascular (CV) and mortality risk [6], which is why the prevention of DKD is a crucial global issue.

To delay the onset and progression of DKD, glycemic, blood pressure, and lipid control targets are set for diabetic patients; additionally, they are provided with advice on lifestyle changes, including nutritional management and exercise, to achieve their recommended targets [3]. Nevertheless, patients who cannot achieve the HbA1c target should be prescribed glycemic control drugs [3]. As sodium-glucose cotransporter 2 inhibitors (SGLT2i) are diabetic drugs that inhibit glucose reabsorption in the proximal renal tubule and promote urinary glucose excretion, they not only improve glycemic control independently of insulin-mediated mechanisms, but are also associated with body weight reduction [7]. Thus SGLT2i are thought to exert their glucose-lowering effect by reducing renal tubular glucose reabsorption, weight, systemic blood pressure, intraglomerular pressure, albuminuria, and slow GFR loss through mechanisms that appear to be independent of glycemia [7].

SGLT2i were first approved for use in 2012 in Europe and then in the US and Japan in 2014. Several SGLT2is are already widely used not only glycemic control but also for the reduction of CV mortality [8] and the incidence and exacerbation of DKD [9]. Although the renoprotective effect of SGLT2i is mainly thought to correct intraglomerular hypertension via restoration of tubular glomerular feedback [7], its mechanism is practically difficult to demonstrate. So far, few studies have attempted to elucidate the mechanisms in type 1 [10] and type 2 [11] diabetic patients; however, both trials enrolled patients with glomerular hyperfiltration. In this trial, we demonstrate how SGLT2i changes renal hemodynamics in DKD patients with moderate renal dysfunction. This renoprotective effect of canagliflozin derived from test of renal hemodynamics in diabetic kidney disease (FAGOTTO) study is expected to provide new evidence on the renoprotective effect of SGLT2i.

## Methods

### Trial design

The FAGOTTO trial is a multicenter, open-label, randomized (1:1), parallel-group study aimed at clarifying the effects of canagliflozin on renal hemodynamics and its safety in patients with type 2 diabetes and moderate DKD. This trial has been registered in the Japan Registry of Clinical Trials (jRCTs041200069). The study protocol was approved by the Certified Review Board of Nagoya University Graduate School of Medicine (No. CRB4180004). All patients will provide written informed consent to participate in this study after they receive information about the purpose of the study as well as the potential risks and benefits. Additional consent will be also confirmed for use of participant data and biological specimens in future ancillary study.

### Enrollment, randomization, and intervention

Participant recruitment has started in December 2020 at Nagoya University Hospital, Kasugai Municipal Hospital and Nagoya Kyoritsu Hospital in the Aichi Prefecture, Japan. The inclusion, exclusion, and termination criteria are listed in Table 1. Patients are being enrolled via a web-based registration and follow-up system organized by the Nagoya University Hospital’s Center for Advanced Medical and Clinical Research, Aichi, Japan. We are randomly allocating patients to two groups: the patients of canagliflozin (100 mg/day) group will receive the trial drug in the morning added to the patients’ usual treatment and the patients of control group will continue the conservative therapy. The allocation ratio is 1:1, and a dynamic allocation strategy using a minimization method is being used. The stratifying factors for randomization are eGFR (> 45 or ≤ 45 mL/min/1.73 m^2^), proteinuria (> 0.5 or ≤ 0.5 g/g Cr), age (> 70 or ≤ 70 years), HbA1c (> 7.0 or ≤ 7.0%), and the trial site.

**Table1 Tab1:** Eligibility criteria

Inclusion criteria
**1.** Stable type 2 diabetes
**2.** eGFR (creatinine) ≤ 60 mL/min/1.73m^2^
**3.** Use of renin angiotensin system inhibitors (exclude intolerable or non-adaptive)
**4.** Age ≥ 18 years
**5.** Provision of written informed consent
Exclusion criteria
**1.** SGLT2 inhibitors administered within 8 weeks before providing informed consent
**2.** eGFR(creatinine) < 30 mL/min/1.73m^2^
**3.** Maintenance dialysis therapy or history of kidney plantation
**4.** Use of diuretics
**5.** Use of both ACEi and ARB (renin inhibitor)
**6.** Active nephritis or kidney disease
**7.** Signs of steroid diabetes
**8.** ALT and AST levels exceeding the facility standard value 2.0 fold
**9.** Heart failure NYHA class 4
**10.** Pregnant or planning pregnancy
**11.** Unsuitable for participation as assessed by attending investigator
Stop criteria
**1.** Withdrawal of consent
**2.** eGFR is dropping below 30 ml/min/1.73 m^2^ and medical decision to discontinue
**3.** Hypoglycemic symptoms and medical decision to discontinue
**4.** Ketoacidosis
**5.** Failure to attend hospital visits
**6.** Patient is found to be ineligible after starting per protocol treatment

### Intervention and control

Eligible participants will be randomly assigned (1:1) to the canagliflozin or control group. After a run-in period of up to 4–8 weeks, the canagliflozin group patients will be administered canagliflozin 100 mg orally once daily in the morning for 12 weeks. In contrast, in the control group, glucose levels will be controlled without any SGLT2i. Inulin and para-aminohippuric acid (PAH) clearance tests for the measurement of renal hemodynamics will be performed at baseline and 4 weeks after the start of the trial. A change in the type or dose of prior diabetic drugs and antihypertensive drugs is prohibited during the 12-week intervention period, but if side effects such as hypoglycemia and hypotension occur, reduction of the dose or discontinuation of these drugs is allowed. The use of the following drugs is restricted during the 12-week intervention period: diuretics, drugs that enhance the hypoglycemic effect, including β-blockers, salicylic acid agents, and monoamine oxidase inhibitors.

The study flowchart is shown in Fig. 1.

**Fig. 1 Fig1:**
[figure not shown]
The study flowchart

### Renal hemodynamic calculation

mGFR and effective renal plasma flow (eRPF) will be calculated using inulin and PAH clearance, respectively. Briefly, 1% inulin and 0.5% PAH will be administered by means of a continuous intravenous infusion for 2 h under overnight fasting but hydrated conditions. If the participants are prescribed diabetic drugs and diuretics, they will be instructed to suspend the use of these drugs. Before infusion, participants will drink 500 ml of tap water in the outpatient treatment room to stimulate diuresis. During infusion, blood samples will be drawn 2 times at 45 and 105 min for measurement of serum levels of inulin and PAH, and urine samples will be collected between 45 and 105 min for measurement of urinary inulin and PAH excretion after completely emptying the bladder 45 min after the start of the infusion.

The filtration fraction (FF), effective renal blood flow (eRBF), and renal vascular resistance (RVR) will be calculated by dividing mGFR by eRPF, eRPF by (1-hematocrit), and mean blood pressure by eRBF, respectively. eGFR from creatinine levels (eGFRcreat) will be calculated as follows: eGFRcreat (mL/min/1.73 m^2^) = 194 × SCr^−1.094^ × Age^−0.287^ (× 0.739: coefficient for female) [12].

### Data collection and other determinant

Baseline characteristics, medication information, vital signs, and biochemical data will be collected. Body weight will be measured at arrival in the clinic (before the inulin clearance test) and blood pressure will be measured twice in the sitting position before and after the inulin clearance test. Measurements of blood urea nitrogen, creatinine, hematocrit, HbA1c, alanine aminotransferase (ALT), aspartate aminotransferase (AST), proteinuria, and albuminuria are planned at baseline, 4–6 weeks after the start of the trial, and at the end of the trial and will be performed using routine procedures at the clinical chemistry facilities of each hospital. Serum and urinary inulin levels will be measured in the laboratory of SRL Inc. (Aichi, Japan). Serum and urinary PAH levels will be measured using liquid chromatography mass spectrometry (LC–MS/MS) at the Institute of Transformative Bio-Molecules (ITbM), Nagoya University, Aichi, Japan. Urinary angiotensinogen levels will be measured using a sandwich ELISA system at the Department of Pharmacology, Kagawa University, Kagawa, Japan. For quality control and quality assurance, a data monitoring committee is composed and monitoring adherence to the protocol. Auditing trial conduct is scheduled and the process will be independent from investigators and the sponsor.

### Endpoints

The primary endpoint of the protocol is the percentage change in FF after 4 weeks of treatment in the canagliflozin and control groups. The secondary endpoints are (1) the change in FF, percentage change, and change in (2) mGFR, (3) eRPF, (4) eRBF, and (5) RVR after 4 weeks of treatment; (6) changes in eGFR, HbA1c, and albuminuria after 4 and 12 weeks of treatment; and (7) trend of blood pressure and body weight after 4 and 12 weeks of treatment in the canagliflozin and control groups. In addition, we plan to (8) compare the changes in urinary angiotensinogen levels between the canagliflozin and control groups after 4 weeks of treatment. Moreover, the rate of adverse drug reactions will be assessed for safety.

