### Statistical analyses

Validity/safety will be analyzed in the largest analysis target group (full analysis set; FAS), defined below. To be included in the FAS, subjects must satisfy these two criteria: (1) meet the selection criteria and not meet the exclusion criteria, and (2) have at least one marker to evaluate efficacy after administration (regardless of the primary or secondary endpoint). The primary aim of the analysis is to compare the percentage changes between the canagliflozin group and the control group at 4 weeks after administration using analysis of covariance (ANCOVA) with eGFR, proteinuria, age, and HbA1c as covariates. No interim analysis is planned.

The analysis methods for secondary outcomes are shown in Table 2.

**Table 2 Tab2:** Analysis methods for secondary outcomes of the canagliflozin and control groups

Secondary outcomes	The analysis methods
1. Percentage change and the change in eRPF, eRBF, and RVR after 4 weeks of treatment	• Compare the percentage changes between the canagliflozin group and the control group at 4 weeks after administration by analysis of covariance (ANCOVA) with eGFR, proteinuria, age and HbA1c as covariates
2. Change in FF, eRPF, eRBF, and RVR after 4 weeks of treatment	• Compare the percentage changes between the canagliflozin group and the control group at 4 weeks after administration by analysis of covariance (ANCOVA) with FF, eRPF, eRBF, and RVR at the baseline and eGFR, proteinuria, age, and HbA1c as covariates
3. Changes in eGFR, HbA1c, albuminuria after 4 weeks and 12 weeks of treatment, trend of blood pressure and body weight after 4 weeks and 12 weeks of treatment, and change in urinary angiotensinogen levels after 4 weeks of treatment	• Calculate the adjusted mean and the 95% CI for changes at each time point by a linear mixed model with each treatment group, time point, and interaction of the treatment group and time point as the fixed effects • Compare between treatment groups using a linear mixed model with values of each index at baseline, treatment groups, time points, interaction between treatment groups and time points as the fixed effects and changes of each index as response variables • Compare changes of each index among treatment groups at each time point using the Tukey–Kramer method to correct for multiplicity
4. Rate of adverse drug reactions	• Calculate the 95% confidence interval for each treatment group and compare it between the groups using χ2 test (or Fisher's exact test)

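### The between-arm safety test uses adverse drug reactions, which depend on unblinded causality judgement in a trial whose controls get no trial drug, so it can be significant with no true excess of events

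*Protocol article*

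**What the plan says.** The Endpoints section names one outcome labelled as safety: "the rate of adverse drug reactions will be assessed for safety". It does not itself mention a comparison. The comparison is in the Statistical analyses section, Table 2, row 4: "Calculate the 95% confidence interval for each treatment group and compare it between the groups using" a chi-square test, with Fisher's exact test as the alternative. The same section sets the population: "Validity/safety will be analyzed in the largest analysis target group (full analysis set; FAS), defined below".

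Three further statements fix the setting:

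- Trial design: "The FAGOTTO trial is a multicenter, open-label, randomized (1:1), parallel-group study".
- Enrollment, randomization, and intervention: "the patients of control group will continue the conservative therapy".
- Intervention and control: "in the control group, glucose levels will be controlled without any SGLT2i".

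No placebo is described. The article does not define an adverse drug reaction, does not say which drug a reaction must relate to, and names no comparison of adverse events regardless of cause.

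**The concern.** Whether a patient has an adverse drug reaction depends on two things: whether an event happens, and whether it is attributed to a drug. Randomisation makes the first comparable between arms. It does nothing for the second when the person judging causality knows that one patient has just started a new drug and the other has not. The same symptom may then count in one arm and not in the other.

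A chi-square or Fisher test on these rates treats them as one outcome measured alike in both arms. A small p-value could be reported as excess harm from canagliflozin when the arms differ only in attribution. In the other direction, a true excess of events judged unrelated would not enter the comparison at all. This matters because the Trial design section gives safety as part of the trial's aim, and row 4 is the only between-arm comparison of adverse events in the article.

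**Working it through.** **Inputs from the article.** Target 55 per arm, at least 50 evaluable, significance level 0.05 (Sample size section); chi-square or Fisher test (Table 2, row 4). The article does not state whether the level is two-sided.

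**The article's own figure first.** No safety rate or safety power is stated, so the only design figure to reproduce is the sample size for the primary endpoint. With a two-sided 0.05 level, power 0.85 and a difference of 0.6 SD:

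n per arm = 2 × (1.960 + 1.036)² / 0.6² = 2 × 8.978 / 0.36 = 49.9, that is 50.

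This matches, so two-sided 0.05 and 55 per arm are used below.

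**How few reactions give significance when controls have none.**

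- Fisher, two-sided, k against 0 with equal arms: p = 2 × C(55, k) / C(110, k). For k = 5, p = 0.057. For k = 6, p = 0.027.
- Uncorrected chi-square for k = 4: 110 × (4 × 55)² / (55 × 55 × 4 × 106) = 4.15, p = 0.042.

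The same thresholds hold at 50 per arm (6 against 0: Fisher p = 0.027; 4 against 0: chi-square p = 0.041). With counts this small Fisher's test would usually be preferred, so its results are taken as the main ones.

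**How often the test rejects when the true event rate is the same in both arms.** The article gives neither an event rate nor attribution shares, so all of these are assumptions. Let e be the true proportion of patients with an event in each arm, and let f1 and f0 be the shares judged drug-related under canagliflozin and in control. The observed reaction rates are then e × f1 and e × f0. The rejection probability is the sum, over all pairs of counts (i, j), of Binomial(i; 55, e × f1) × Binomial(j; 55, e × f0), taken where p < 0.05. This is exact enumeration, not simulation.

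With e = 30% and f1 = 50%, the canagliflozin reaction rate is 15%:

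| Share attributed in control (f0) | Control reaction rate | Fisher rejects | Chi-square rejects |
|---|---|---|---|
| 0% | 0% | 85% | 97% |
| 10% | 3% | 46% | 63% |
| 25% | 7.5% | 14% | 23% |
| 50% (equal) | 15% | 2.5% | 4.9% |

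Other assumed values, Fisher's test:

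| e | f1 | f0 = 0% | f0 = 10% |
|---|---|---|---|
| 20% | 30% | 11% | 4% |
| 20% | 50% | 48% | 23% |
| 40% | 30% | 66% | 20% |
| 40% | 50% | 98% | 66% |

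The true event rates are equal throughout, so every rejection above the equal-attribution row comes from unequal attribution.

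**The same test on all events.** Setting f1 = f0 = 100% with e from 20% to 40%, Fisher's test rejects 2.7% to 3.1% of the time and chi-square 5.0% to 5.1%. The tests behave properly once the outcome no longer depends on attribution.

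**The case against.** The strongest reply is that controls are not free of drugs. They stay on diabetic and antihypertensive treatment, and the article foresees trouble from it without limiting this to one arm: "if side effects such as hypoglycemia and hypotension occur, reduction of the dose or discontinuation of these drugs is allowed". The renal measurements also give every patient infusions to which they might react: "1% inulin and 0.5% PAH will be administered by means of a continuous intravenous infusion for 2 h". Table 2 plans a confidence interval for each group, which suggests that reactions are to be counted in controls too.

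This stands. A reader might infer that the control rate is zero by definition, but the article does not support that: it never ties the term to canagliflozin. The rate is structurally zero only if the full protocol, which is not shown, defines it that way.

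Three further limits also stand:

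- The 85% figure rests on no attribution at all in controls. It is the upper end of its scenario, not the expected value.
- A reader might infer that events are recorded less carefully in controls. Nothing in the article says so, and collection procedures are commonly left to the full protocol.
- A reader might infer that nothing else in the plan bears on safety. Changes in eGFR and blood pressure are compared between arms (Table 2, row 3), and they do not depend on causality judgement.

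The reply does not rescue row 4. If the term means reactions to canagliflozin, the control rate is fixed at zero and the test says nothing about excess harm. If it means reactions to any drug, the comparison rests on unblinded judgement, with a new drug available as an explanation in one arm only. The point concerns an outcome and a test that the article states, so it is not a complaint about omitted detail.

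**Conclusion.** The point holds in this form: row 4 tests a causality-dependent rate between the arms of an open-label trial without placebo, so it can be significant with no true excess of events. The thresholds of 6 against 0 (Fisher) and 4 against 0 (uncorrected chi-square) depend only on the arm size. The probability of a misleading result does not have a single value. Under a 30% event rate and 50% attribution with canagliflozin, it runs from 85% with no control attribution down to the nominal 2.5% when attribution is equal. Where the trial falls in that range depends on the definition of a reaction and on how investigators apply it, and the article shows neither.

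Severity is moderate. This is a secondary safety analysis with no stated power; the primary endpoint, its analysis and the sample size are untouched. It would be too strong to say that the trial's main conclusion is at risk.

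**What to change.** In Table 2, row 4, make the between-arm safety comparison on all adverse events regardless of causality, with serious adverse events and hypoglycaemia shown in the same way. Report the risk difference with its 95% CI. Keep adverse drug reactions as a descriptive count and proportion in each arm, without a test. Do not drop the control arm from that table, because reactions to background drugs or to the infusions would be lost. State in the same row which drugs a reaction may be attributed to.

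The cost is a change of wording before analysis and a little extra tabulation. It needs adverse events to be available for both arms whatever the causality judgement; the article does not show whether they already are.

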### Sample size

For the purpose of comparing independent results, we decided to use power of 0.85 and a significance level of 0.05, to detect a significant difference. The difference in the percentage change in FF after 4 weeks of treatment in the canagliflozin group compared with that in control group was assumed to be 60% of the standard deviation. Based on these calculations, we determined that at least 50 individuals are necessary for each group. Taking into account potential discontinuation and withdrawal, we set the target number for the canagliflozin group to 55, with 55 control patients, and thus, 110 patients were planned to be included in total. Additionally, we took into account the actual number of patients who met the registration criteria at each facility.

### Statistical analyses

Validity/safety will be analyzed in the largest analysis target group (full analysis set; FAS), defined below. To be included in the FAS, subjects must satisfy these two criteria: (1) meet the selection criteria and not meet the exclusion criteria, and (2) have at least one marker to evaluate efficacy after administration (regardless of the primary or secondary endpoint). The primary aim of the analysis is to compare the percentage changes between the canagliflozin group and the control group at 4 weeks after administration using analysis of covariance (ANCOVA) with eGFR, proteinuria, age, and HbA1c as covariates. No interim analysis is planned.

The analysis methods for secondary outcomes are shown in Table 2.

**Table 2 Tab2:** Analysis methods for secondary outcomes of the canagliflozin and control groups

Secondary outcomes	The analysis methods
1. Percentage change and the change in eRPF, eRBF, and RVR after 4 weeks of treatment	• Compare the percentage changes between the canagliflozin group and the control group at 4 weeks after administration by analysis of covariance (ANCOVA) with eGFR, proteinuria, age and HbA1c as covariates
2. Change in FF, eRPF, eRBF, and RVR after 4 weeks of treatment	• Compare the percentage changes between the canagliflozin group and the control group at 4 weeks after administration by analysis of covariance (ANCOVA) with FF, eRPF, eRBF, and RVR at the baseline and eGFR, proteinuria, age, and HbA1c as covariates
3. Changes in eGFR, HbA1c, albuminuria after 4 weeks and 12 weeks of treatment, trend of blood pressure and body weight after 4 weeks and 12 weeks of treatment, and change in urinary angiotensinogen levels after 4 weeks of treatment	• Calculate the adjusted mean and the 95% CI for changes at each time point by a linear mixed model with each treatment group, time point, and interaction of the treatment group and time point as the fixed effects • Compare between treatment groups using a linear mixed model with values of each index at baseline, treatment groups, time points, interaction between treatment groups and time points as the fixed effects and changes of each index as response variables • Compare changes of each index among treatment groups at each time point using the Tukey–Kramer method to correct for multiplicity
4. Rate of adverse drug reactions	• Calculate the 95% confidence interval for each treatment group and compare it between the groups using χ2 test (or Fisher's exact test)

*ANCOVA* Analysis of covariance, *FF* Filtration fraction, *eRPF* Effective renal plasma flow, *eRBF* Effective renal blood flow, *RVR* Renal vascular resistance

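### A single analysis set for efficacy and safety can drop treated patients from the adverse drug reaction rate, and lets randomised patients be removed for ineligibility without a blind, pre-randomisation rule

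*Protocol article*

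**What the plan says.** The Statistical analyses section of the protocol article names one population for both purposes: "Validity/safety will be analyzed in the largest analysis target group (full analysis set; FAS), defined below". It sets two conditions of entry. The first is that a patient must "meet the selection criteria and not meet the exclusion criteria". The second is that the patient must "have at least one marker to evaluate efficacy after administration (regardless of the primary or secondary endpoint"). No other safety denominator is given, and the adverse drug reaction row of Table 2 names no population of its own.

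Four other statements bear on how these conditions work:

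- **Timing of markers.** The Intervention and control section places the clearance tests at baseline and week 4. The laboratory measurements are "planned at baseline, 4–6 weeks after the start of the trial, and at the end of the trial" (Data collection and other determinant). The secondary endpoints, including blood pressure and body weight, are set at weeks 4 and 12.
- **Reasons to stop (Table 1).** Stop criterion 3 reads "Hypoglycemic symptoms and medical decision to discontinue"; stop criterion 4 is ketoacidosis. Stop criterion 6 reads "Patient is found to be ineligible after starting per protocol treatment".
- **Subjective eligibility (Table 1).** Exclusion criterion 11 reads "Unsuitable for participation as assessed by attending investigator".
- **Design.** The trial is open-label, and the article describes assignment first, then a run-in, then the 12-week intervention period.

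**The concern.** A safety rate should count everyone exposed. Here, whether a reaction is counted depends on two things unrelated to exposure: whether an efficacy marker exists, and whether the patient is held to be eligible. Hypoglycaemia and ketoacidosis are foreseen as reasons to stop, and a stop can come before week 4. If such a patient has no later marker, the reaction that ended treatment is not in the reported rate. A treated patient later found ineligible is also lost from safety, although exposed.

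The efficacy side raises a different question. The eligibility condition allows a randomised patient to be taken out of the comparison. The article does not say that this must rest on facts dated before randomisation, or be decided without knowledge of the arm. Allocation is open, one exclusion is the attending investigator's opinion, and the stop rules expect some ineligibility to come to light after treatment has begun. At stake are the credibility of the between-group comparison of adverse drug reactions and, to a lesser degree, the protection that randomisation gives the primary comparison.

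**Working it through.** **1. The plan's own numbers, for scale.** From the Sample size section: power 0.85, significance level 0.05 (taken as two-sided), difference 0.6 SD.

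n per arm = 2 × (1.960 + 1.036)² / 0.6² = 2 × 8.976 / 0.36 = 49.9, so 50. This matches the article. The target of 55 allows for 5 losses per arm (5/55 = 9.1%). The article does not say that these losses would be patients with no marker at all, so 5 serves below only as an upper illustration.

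**2. Who is lost under the rule as written.**

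| Patient | In the adverse drug reaction rate? | In the week-4 FF ANCOVA? |
|---|---|---|
| Dosed, stops before week 4, no post-start marker of any kind | No (condition 2) | No: there is no week-4 FF under any set definition |
| Dosed, stops early, but has some post-start marker | Yes, if that marker counts | Only if week-4 FF was measured |
| Treated, later found ineligible | No (condition 1) | No, even if week-4 FF was measured |

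Condition 2 therefore matters for safety. Condition 1 matters for safety and for efficacy.

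**3. Safety rate.** Let the set contain n patients with x reactors, and let k patients with e reactors be lost. The reported rate is x/n and the full rate is (x + e)/(n + k). The reported rate is too low when e/k > x/n and too high when e/k < x/n. The document gives no event counts, so every count below is an assumption.

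*Lost patients are all reactors.* Assume 10/55 on canagliflozin (18.2%) and 3/55 on control (5.5%); Fisher's exact p = 0.073.

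| Reactors lost from the canagliflozin arm | Reported rate | p against 3/55 |
|---|---|---|
| 1 | 9/54 = 16.7% | 0.073 |
| 3 | 7/52 = 13.5% | 0.194 |
| 5 | 5/50 = 10.0% | 0.474 |

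*Lost patients have no reaction.* Assume 8 reactors among 55, and 5 non-reactors lost. The reported rate is 8/50 = 16.0% against a full rate of 8/55 = 14.5%, an error in the other direction.

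**4. Efficacy comparison under condition 1.** Suppose k of 55 patients are removed from one arm and their mean differs by g SD from those kept. The arm mean then moves by (k/55) × g. Both k and g are assumptions.

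- k = 1, g = 0.5: 1/55 × 0.5 = 0.009 SD, which is 1.5% of the planned 0.6 SD.
- k = 3, g = 1.0: 3/55 × 1.0 = 0.055 SD, 9.1%.
- k = 5, g = 1.0: 5/55 × 1.0 = 0.091 SD, 15.2%.

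These figures take all removals from one arm. Equal removal of similar patients from both arms would largely cancel.

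**The case against.** The strongest reply is that the rule is lenient and the harm hypothetical.

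- **Any marker is enough.** A primary or secondary marker qualifies, and blood pressure, weight and eGFR are on the list. The text does not exclude unscheduled values, and a stop for a fall in eGFR itself needs a post-start eGFR. This stands: only patients with no marker at all are lost. A reader might infer that every early toxicity stop disappears; the article does not support that.
- **The direction is not fixed.** Early leavers also include withdrawals of consent and missed visits. This stands. A reader might infer that the canagliflozin rate must come out too low; step 3 shows that it can go either way.
- **Condition 2 does not bias the primary analysis.** A patient with no post-start marker has no week-4 FF and could enter the ANCOVA only by imputation. This stands.
- **Nothing says eligibility is reopened with the response known.** Exclusion 11 is an enrolment criterion, stop criterion 6 governs stopping treatment, and inulin and PAH are assayed away from the attending clinicians. This stands in part: knowledge of the FF response cannot be assumed. But allocation is open, and the article puts no safeguard on how or when condition 1 is applied.
- **The reference to administration can be read as the start of the intervention period,** since the article uses it for the week-4 comparison of both arms. This stands. A reader might infer that the rule cannot be applied to controls at all; that goes too far, though the wording is loose for an arm that receives no trial drug.
- **A fuller document may define a safety set.** That would answer an omission. Here the article states which set is used for safety, and that statement is the problem.

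**Conclusion.** The point holds in limited form and should be fixed before the data are analysed. As written, dosed patients who stop before week 4 with no post-start marker, and treated patients later found ineligible, are left out of the adverse drug reaction rate. The rate can be distorted and can miss reactions that ended treatment. Neither direction nor size can be computed from the document. Under the assumed counts the error runs from 1.5 percentage points too low (one reactor lost) to 8.2 points too low (five lost), or 1.5 points too high if five non-reactors are lost.

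Separately, the eligibility condition can bias the open-label efficacy comparison because it is not tied to pre-randomisation facts judged blind to arm. The illustrative shift is 0.009 to 0.091 SD, or 1.5% to 15% of the planned effect, assuming one-sided removal of 1 to 5 patients who differ by 0.5 to 1.0 SD. This is a possible bias, not a demonstrated one. It does not invalidate a 12-week mechanistic trial whose primary endpoint is FF.

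**What to change.** 1. **Define a safety set** with no efficacy-data condition and no eligibility condition. Start membership and event counting from the same time zero in both arms, the start of the 12-week intervention period: canagliflozin patients with at least one dose, and controls who reached the corresponding start. Taking all randomised controls against only dosed canagliflozin patients would be unequal, because patients can leave between assignment and first dose.
2. **Analyse efficacy in all randomised patients as allocated.** If eligibility exclusions are kept, limit them to objective facts dated before randomisation and decided without knowledge of allocation. Exclusion criterion 11 should not be a ground for removal.
3. **Reword condition 2, wherever its timing phrase is kept,** so that it refers to the start of the intervention period in both arms.

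The cost is wording in the protocol and analysis plan; the target of 55 per arm is unchanged. A few ineligible patients may stay in and slightly dilute the estimate. The change does not supply week-4 FF for patients who lack it, so how those patients are handled still has to be settled in the analysis plan.
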